#### 9.1.1.7 Pentaglobin

Immunoglobulins are normal components of the human body. The determination of acute toxicity in animals is of no relevance since higher doses lead to circulatory overload. Chronic toxicity and embryo-fetal toxicity studies cannot be performed due to induction and interference with antibodies.

Experimental studies on animals are not considered necessary.

#### Contraindications

- Hypersensitivity to the active substance (human immunoglobulin) or to any of the excipients listed in section 6.1.
- Patients with selective IgA deficiency who have developed antibodies against IgA, since the administration of a preparation containing IgA can lead to anaphylaxis.

#### Risks:

From a medical point of view, the risk of infection from viruses is so low that there is no additional testing in this context.

#### Summary of the security profile

Side effects caused by normal human immunoglobulins (ordered by decreasing frequency) include (see also section 4.4):

- Chills, headache, dizziness, fever, vomiting, allergic reactions, nausea, joint pain, low blood pressure and moderate lower back pain
- reversible hemolytic reactions; especially in patients with blood groups A, B and AB and (in rare cases) haemolytic anemia requiring transfusion

- (in rare cases) a sudden drop in blood pressure and, in individual cases, anaphylactic shock, even if the patients have not shown hypersensitivity with previous use
- (in rare cases) transient skin reactions (including cutaneous lupus erythematosus - frequency not known)
- (in very rare cases) thromboembolic reactions such as heart attack (myocardial infarction), stroke, blood clot in blood vessels in the lungs (pulmonary embolism), blood clot in a vein (deep venous thrombosis)
- Cases of reversible aseptic meningitis
- Cases of an increase in serum creatinine and / or acute kidney failure
- Cases of transfusion-associated acute lung insufficiency (TRALI)

Tab. 1 side effects from clinical studies

| System Organ Class (SOC) according to MedDRA          | Side effects                              | Frequency    |
|-------------------------------------------------------|-------------------------------------------|--------------|
| Immune system disorders                               | Allergic reaction                         | occasionally |
| Vascular disorders                                    |                                           |              |
|                                                       | Hypotonia                                 | often        |
| Gastrointestinal symptoms                             | Nausea and vomiting                       | occasionally |
| Skin and subcutaneous tissue disorders                | Hyperhidrosis                             | often        |
|                                                       | Cutaneous reactions / allergic dermatitis | occasionally |
| Skeletal muscles, connective tissue and Bone diseases | Back pain                                 | occasionally |

Tab. 2 Side effects from post marketing observations

| System organ classes (SOC) according to MedDRA       | Side effects                                                      |
|------------------------------------------------------|-------------------------------------------------------------------|
| Infections and parasitic diseases                    | Aseptic meningitis                                                |
| Blood and lymphatic system disorders                 | Haemolytic anaemia                                                |
| Immune system disorders                              | Anaphylactic shock, anaphylactoid reactions, hypersensitivity     |
| Nervous system disorders                             | Headache, dizziness                                               |
| Heart disease                                        | Tachycardia                                                       |
| Vascular diseases                                    | Flush                                                             |
| Respiratory disorders, Chest and mediastinum         | Dyspnea                                                           |
| Diseases of the skin and the Subcutaneous tissue     | Pruritus                                                          |
| Kidney and urinary disorders                         | Acute kidney failure and / or increase in serum creatinine levels |
| General disorders and administration site complaints | Fever, chills                                                     |

### 9.1.2 Definition of adverse events

An AE is any untoward adverse change from the subject's baseline condition, i.e., any unfavorable and unintended sign including an abnormal laboratory finding, symptom or disease which is considered to be clinically relevant by the physician that occurs during the course of the study, whether or not considered related to the study drug.

Adverse events include:

- Exacerbation of a pre-existing disease.
- Increase in frequency or intensity of a pre-existing episodic disease or medical condition.
- Disease or medical condition detected or diagnosed after study drug administration even though it may have been present prior to the start of the study.
- Continuous persistent disease or symptoms present at baseline that worsen following the start of the study.
- Lack of efficacy in the acute treatment of a life-threatening disease.
- Events considered by the Investigator to be related to study-mandated procedures.
- Abnormal assessments, e.g., ECG and physical examination findings, must be reported as AEs if they represent a clinically significant finding that was not present at baseline or worsened during the course of the study.
- Laboratory test abnormalities must be reported as AEs if they represent a clinically significant finding, symptomatic or not, which was not present at baseline or worsened during the course of the study or led to dose reduction, interruption or permanent discontinuation of study drug.

Adverse events do not include:

- Pre-planned interventions or occurrence of endpoints specified in the study protocol are not considered AE's, if not defined otherwise (eg.as a result of overdose)
- Medical or surgical procedure, e.g., surgery, endoscopy, tooth extraction, transfusion. However, the event leading to the procedure is an AE. If this event is serious, the procedure must be described in the SAE narrative.
- Pre-existing disease or medical condition that does not worsen.
- Situations in which an adverse change did not occur, e.g., hospitalizations for cosmetic elective surgery or for social and/or convenience reasons.
- Overdose of either study drug or concomitant medication without any signs or symptoms. However, overdose must be mentioned in the Study Drug Log.

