|  | 
 
▪ Time to discharge or to a NEWS of <math>\leq 2</math> and maintained for 24 hours, whichever occurs first
 
▪ Change from baseline (assessment once daily)
 
- Oxygenation 
 
▪ Oxygenation free days until day 29
 
▪ Incidence and duration of new oxygen use (e.g. oxygen insufflation, high-flow oxygen, non-invasive ventilation, mechanical ventilation, etc.) during the trial
 
 
 
- Viral clearance
 
- Duration of hospitalization, of ICU treatment and number of ICU admissions
 
- Mortality at day 15, 29, day 60 and day 90
 
- Sub-Study A: number of thromboembolic events
 
- Sub-study B: To investigate the RAS and bradykinin fingerprint of patients with SARS-CoV-2 infection, with and without RAS blocking treatment, as specified above; to investigate blood pressure, dyspnea, body temperature, fear/anxiety (subject to availability of samples)
 
- Within all patients, the impact of obesity and associated diseases on mortality will be investigated (e.g. mortality, inflammatory response, duration of hospitalization, intensive care unit admission, new oxygen use, duration of oxygen)
 
- Exploratory assessment of transaminases (including alkaline phosphatase, gamma-glutamyltransferases (GGT), aspartate aminotransferase (ASAT), alanine aminotransferase (ALAT)) and liver function parameters (including bilirubin, prothrombin time, international normalized ratio, albumin, fibrinogen) and their course during the disease and treatment
 
- An exploratory endpoint will encompass a comprehensive assessment of inflammatory parameters and their changes during treatment and wash out time, as well as exploratory genotype and RNA analysis with a focus on inflammation, coagulation, and the specific pathophysiology of the disease (if possible for center).
 
- Sub-study C: modified SOFA score, <math>paO_2/FiO_2</math> ratio, or <math>SpO_2/FiO_2</math> ratio
 
- Substudy C, Pentaglobin part: CRP, PCT, IL-6, differential blood count (baseline and day 2, 3, 7), IgM, IgA and IgG levels (baseline, day 2, 3, 4, 5), modified SOFA score (baseline, day 7 and day 28)
 
 |

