## 9.2 Serious adverse events (SAEs)

A Serious Adverse Event (SAE) is defined by the International Conference on Harmonization (ICH) guidelines and GCP guidelines as any AE fulfilling at least one of the following criteria:

- Results in deaths.
- Life-threatening – defined as an event in which the subject was, in the judgment of the Investigator, at risk of death at the time of the event;
- Requiring subject's hospitalization or prolongation of existing hospitalization
- Resulting in persistent or significant disability or incapacity (i.e., a substantial disruption of a person's ability to conduct normal life functions).
- Congenital anomaly or birth defect.

- Optional: Is medically significant or requires intervention to prevent at least one of the outcomes listed above

Life-threatening refers to an event in which the subject was at risk of death at the time of the event. It does not refer to an event that hypothetically might have caused death if it were more severe.

Important medical events that may not immediately result in death, be life-threatening, or require hospitalization may be considered as SAEs when, based upon appropriate medical judgment, they may jeopardize the subject and may require medical or surgical intervention to prevent one of the outcomes listed in the definitions above. This means an individual case decision.

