### 11.6.2 Secondary endpoint analysis

- Clinical Status of patients according to the above-mentioned WHO scale:
  - Time to improvement of one category from admission
  - Clinical status daily
  - Mean change in the ranking on an ordinal scale from baseline
- National Early Warning Score (NEWS):
  - Time to discharge or to a NEWS of  $\leq 2$  and maintained for 24 hours, whichever occurs first
  - Change from baseline
- Oxygenation
  - Oxygenation free days until day 29
  - Incidence and duration of new oxygen use during the trial
- Mechanical Ventilation
  - Ventilator free days until day 29
  - Incidence and duration of new mechanical ventilation use during the trial
- Viral load/viral clearance
  - Baseline, and three times a week until infection has resolved
- Hospitalization
  - Duration of hospitalization
  - Duration of intensive care unit treatment
  - Intensive care unit admissions
- Mortality
  - 15-day, 29-, 60-day mortality
- Within all patients, the impact of obesity and associated diseases on mortality will be investigated (e.g. mortality, inflammatory response, duration of hospitalization, intensive care unit admission, new oxygen use, duration of oxygen)
- Treatment arm 2: drug-drug interaction analysis with lopinavir/ritonavir, in a retrospective manner
- pharmacokinetics of antiviral substances, if assays are available (e.g. lopinavir/ritonavir trough level analysis)
- Sub-study A: thromboembolic events

- Sub-study B: Renin Angiotensin System (RAS) fingerprint in patients with SARS-CoV-2 infection randomized to no RAS blocking agents, randomized to angiotensin converting enzyme (ACE) inhibitor treatment and randomized to angiotensin II blockade
  - Quality of life: EuroQoL- 5 Dimension (EQ-5D)
  - Activities of daily living/life participation, Instrumental activities of daily living scale (IADLS)
  - PROMIS social function measures
  - Dizziness
  - Gastrointestinal symptoms including nausea and vomiting (PROMIS gastrointestinal symptom scales)
  - Gastrointestinal symptom rating scale (before respiratory symptoms, many patients with COVID-19 had diarrhea, nausea, vomiting, abdominal discomfort)
  - Headache: headache impact test 6-item (HIT-6)
  - Anxiety: hospital anxiety and depression scale (HADS)
  - Fear/anxiety reported with SARS-CoV-2 infection (qualitative interview at baseline and recovery, GAD-7 scale value at all study visits [telephone or in person])

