### **11.6.3 Safety and tolerability endpoints**

- Cumulative incidence of serious adverse events
- Discontinuation or temporary suspension of therapy
- Changes in white cell count, hemoglobin, platelets, creatinine, glucose, total bilirubin, alanine aminotransferase (ALT), aspartate aminotransferase (AST) over time
- Occurrence of drug induced liver injury (DILI) in various treatment arms
- Bleeding events

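### The adverse-event definition exempts protocol endpoints without naming them, so whether deaths and sub-study A bleeding and thromboembolic events count as SAEs is unresolved

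*Protocol*

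**What the plan says.** Among the things that are not adverse events, section 9.1.2 lists: "Pre-planned interventions or occurrence of endpoints specified in the study protocol are not considered AE's, if not defined otherwise (eg.as a result of overdose"). The operative words are "occurrence of endpoints specified in the study protocol are not considered" AEs, and the only illustration of an exception is overdose.

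Section 9.2 defines an SAE as "any AE fulfilling at least one of the following criteria", and the first criterion is "Results in deaths". Section 9.2.1 applies the same logic to certain hospital stays: because they are not AEs, they are not SAEs either.

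The protocol's endpoints include:
- "Mortality at day 15, 29, day 60 and day 90" (synopsis);
- "Sub-study A: thromboembolic events" (section 11.6.2);
- bleeding events (synopsis and sections 6.2 and 11.6.3);
- "Occurrence of drug induced liver injury (DILI) in various treatment arms" (section 11.6.3);
- laboratory changes over time, and the cumulative incidence of SAEs (section 11.6.3).

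Section 9.1.2 also lists what is an AE. The list includes "Lack of efficacy in the acute treatment of a life-threatening disease", exacerbation of existing disease, and clinically significant laboratory abnormalities, which it makes mandatory to report.

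**The concern.** Exempting endpoint events from AE reporting is common when the endpoint is expected disease progression that is captured elsewhere. Here the exemption has no such limit. It covers whatever the protocol lists as an endpoint, and that list includes harms a study drug may cause. Section 9.1.1.4 calls bleeding the main risk of rivaroxaban, and bleeding is a sub-study A endpoint.

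Two things are at stake. First, cumulative SAE incidence is the first safety endpoint in section 11.6.3, and its content depends on how each site reads one bullet. The trial is open label (section 8.3) and multicentre, and monitoring reviews only primary endpoint data (section 12.3.1), so divergent practice might not be noticed. The synopsis expects centres to have access to different arms, so differences between sites could also show up as differences between arms. Second, a SUSAR report under section 9.5.2 starts from an adverse event. An event that a site has classed as not an AE may never be assessed for expedited reporting.

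**Working it through.** No sample size, power or error rate is involved, so the check sets the sections side by side.

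**The chain.** (1) Section 9.1.2: an endpoint event is not an AE unless defined otherwise. (2) Section 9.2: only an AE can be an SAE. (3) Section 9.5.2: a SUSAR report concerns an adverse event that is serious and unexpected. An exempted event therefore drops out at all three levels. Death as a seriousness criterion does not break the chain, because it is applied to something already accepted as an AE.

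**Event by event.**
- *Bleeding (sub-study A).* It is a listed endpoint, so it is exempt on a literal reading. No text names bleeding as an AE despite its endpoint status.
- *Thromboembolic events (sub-study A).* The result is the same: a listed endpoint, with no text restoring it by name.
- *Death.* Mortality is a listed endpoint, so death is exempt on a literal reading. Against this, section 9.1.2 counts lack of efficacy in a life-threatening disease and worsening disease as AEs, the AE form in section 9.5 has a fatal outcome category, and section 9.5.2 sets 7 calendar days for fatal or life-threatening SUSARs. The protocol thus both exempts and expects such reports.
- *Liver injury and laboratory changes.* These are listed endpoints, but section 9.1.2 expressly requires clinically significant laboratory abnormalities to be reported as AEs. That can fairly be read as the otherwise-defined case, so the exemption has least force here.

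**Does the qualifier settle it?** Only for events that some other text defines as AEs by type. That works for laboratory findings and arguably for fatal COVID-19 progression. It does not work for bleeding or thromboembolism. The general AE definition would cover them, but the exemption is a carve-out from that general definition.

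**Is a literal reading workable?** No. Cumulative SAE incidence is an endpoint in section 11.6.3. Taken at its word, the clause would exempt every SAE because it is the occurrence of an endpoint. A site must therefore supply its own limit, and the protocol gives none and no rule of precedence between the two lists in section 9.1.2.

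**The case against.** The strongest reply is that the literal reading plainly cannot be intended. The bullet carries a qualifier, the same section makes several of these events AEs, and section 9.5 is written for fatal AEs and fatal SUSARs. A sensible investigator would report a drug-related fatal bleed. Nothing is lost to the analysis either: bleeding and liver injury are safety endpoints in their own right, mortality is collected at four time points, and thromboembolic events are counted in sub-study A.

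Much of this stands, and it rules out several stronger readings that a reader might infer:
- *That these events vanish from safety reporting altogether.* They do not. What is unclear is AE, SAE and SUSAR classification and the SAE count.
- *That liver injury is removed.* The laboratory bullet largely covers it.
- *That the SAE endpoint would miss the main harms of every study drug.* Section 9.1.1 does not bear this out. The common effects listed for lopinavir/ritonavir are mainly gastrointestinal and lipid changes, and those for remdesivir are nausea and raised transaminases. For immunoglobulin, haemolysis, anaphylactic shock and aseptic meningitis are listed, and none of these is an endpoint. Rivaroxaban bleeding is the clear case.
- *That every thromboembolic event in the platform is exempt.* It is an endpoint only of sub-study A, and the clause does not say whether it reaches patients outside that sub-study.
- *That the interim safety decisions rest on the SAE count.* Section 11.7 says that arms may be closed for safety and leaves details to the DMC charter, which is not shown.

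What the reply does not remove is the contradiction. That the literal reading is unlikely to be meant does not tell sites which reading is meant, and no text restores bleeding or thromboembolism by name.

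**Conclusion.** The point holds as an unresolved internal contradiction in the AE definition. It is not an established removal of events. The exemption in section 9.1.2 is not confined to named efficacy endpoints and is inherited by the SAE and SUSAR definitions. It conflicts with the AE inclusions in its own section, with section 9.5, and with SAE incidence being an endpoint. The events exposed are deaths and sub-study A bleeding and thromboembolic events that would otherwise meet a criterion in section 9.2.

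Its size cannot be given as a number. A reader might take the 1% to 15% mortality in section 8.4 as the share of patients affected, but that is a range for COVID-19 in general, dependent on the statistical approach, and not an assumption about this hospitalised, oxygen-requiring population. In direction, a site that applies the clause literally reports fewer SAEs than one that does not.

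The conclusion assumes that no site instruction outside the protocol resolves the clause. The definition governs what sites report, so it belongs in the protocol and not in a statistical analysis plan. The primary endpoint analysis, its error rate and its power are not affected.

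**What to change.** Amend the endpoint bullet in section 9.1.2:
- List by name the efficacy endpoints that reflect expected COVID-19 progression and are exempt, and exempt them only when a relation to study drug is not suspected.
- State that the safety endpoints (bleeding, drug-induced liver injury, clinically significant laboratory changes) and thromboembolic events are not exempt, and are SAEs when they meet a criterion in section 9.2.
- State how deaths are counted in the SAE endpoint. Whether every death already captured as mortality is also an SAE is for the sponsor to decide, but the rule must be explicit, and any death suspected to be drug-related must always be reportable.
- Reconcile sections 9.1.2, 9.2, 9.5 and 11.6.3 with the amended bullet.

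The cost is one amended bullet with matching edits, and somewhat more SAE reporting at sites.

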## 9.2 Serious adverse events (SAEs)

A Serious Adverse Event (SAE) is defined by the International Conference on Harmonization (ICH) guidelines and GCP guidelines as any AE fulfilling at least one of the following criteria:

- Results in deaths.
- Life-threatening – defined as an event in which the subject was, in the judgment of the Investigator, at risk of death at the time of the event;
- Requiring subject's hospitalization or prolongation of existing hospitalization
- Resulting in persistent or significant disability or incapacity (i.e., a substantial disruption of a person's ability to conduct normal life functions).
- Congenital anomaly or birth defect.

- Optional: Is medically significant or requires intervention to prevent at least one of the outcomes listed above

Life-threatening refers to an event in which the subject was at risk of death at the time of the event. It does not refer to an event that hypothetically might have caused death if it were more severe.

Important medical events that may not immediately result in death, be life-threatening, or require hospitalization may be considered as SAEs when, based upon appropriate medical judgment, they may jeopardize the subject and may require medical or surgical intervention to prevent one of the outcomes listed in the definitions above. This means an individual case decision.

### 9.2.1 Hospitalization – Prolongation of existing hospitalization

Hospitalization is defined as an overnight stay in a hospital unit and/or emergency room.

An additional overnight stay defines a prolongation of existing hospitalization.

The following is not considered an SAE and should be reported as an AE only:

- Treatment on an emergency or outsubject basis for an event not fulfilling the definition of seriousness given above and not resulting in hospitalization.

The following reasons for hospitalizations are not considered AEs, and therefore not SAEs:

- Hospitalizations for cosmetic elective surgery, social and/or convenience reasons.
- Elective treatment of a pre-existing disease or medical condition that did not worsen, e.g., hospitalization for chemotherapy for cancer, elective hip replacement for arthritis.

